## Method/design

### Study design

This is a prospective, randomised, placebo-controlled, cross-over, double-blind, single-centre study over a period of 36 months.

Each patient included will participate in three visits.

Visit 1 (V1): inclusion and baseline assessment visit. Patients who fulfil all the inclusion and non-inclusion criteria and who have signed informed consent will be included in the study. During this visit, all the clinical and functional evaluations, the instrumented gait analysis and instrumented balance task will be carried out. The patient will also complete all the clinical scales and self-evaluation questionnaires. Furthermore, blood samples will be taken in order to carry out genetic studies and identify carriers of the Val66Met polymorphism in the brain-derived neurotrophic factor gene, since Val66Met reduces the effects of all types of non-invasive brain stimulation [48, 49].

Visits 2 and 3 locomotion/balance (V2 and V3): anodal tDCS or placebo visits. During these visits, before the cortical stimulation (anodal or placebo), all the functional and clinical data will be collected. A 3D gait analysis and instrumented balance task will be carried out before and during the 30 min of stimulation, as well as immediately after the end of the stimulation and 30 min later. Functional and clinical data will be collected again following the stimulation. The order of the placebo and anodal tDCS visits will be randomised. The visits will be 7 days apart. The study schedule is shown in Fig. 1 and the evaluations conducted during the three visits are shown in Table 1.

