### Primary outcomes

#### Before, during, immediately after, and 30 min after tDCS cessation

Variability of the COM

As previously indicated, the variability of COM displacement is a strong marker of dynamic stability during locomotion and it is altered in patients with stroke.

The primary outcome measure of this study is thus the assessment of the variability of the displacement of the COM during gait and during trajectory tracking over the ground, evaluated by 3D gait analysis and the variability of the displacement of the COP during a static-balance task on a force platform. It will be recorded once during the inclusion visit then four times during the stimulation visits: before, during, immediately after and 30 min after cessation of stimulation. A reduction in the variability of COM displacement should result in an improvement of spatiotemporal, kinematic and kinetic gait parameters.

The 3D gait analysis will be conducted with a 3D optoelectronic system (Motion Analysis Corporation, Santa Rosa, CA, USA, sampling frequency 100 Hz) with eight optoelectronic cameras. Thirty markers will be placed on the patient’s body (following the Helen Hayes model commonly used by the biomechanical community for gait analysis [53]). The relative displacement of each segment will be calculated from these coordinates (flexion/extension, abduction/adduction, internal/external rotation). The marker trajectories will then be filtered using a fourth-order zero-lag Butterworth low-pass-filter, with a 6-Hz cut-off frequency [54]. The data from two force platforms combined with the kinematic and anthropometric data will be used to evaluate the displacement of the COP and COM during gait and balance tasks.Instrumented gait task

Ten trials of gait at a comfortable speed and 10 trials at maximal speed will be recordedInstrumented balance task

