### Statistical analysis

The details of calculation of the COM and the COP are available in the ‘Appendix’ section.

The sample size was calculated from the data by Bonnyaud et al. (2016) [24]. Bonnyaud et al. [24] studied the raw trajectory length of patients with hemiparesis compared to a group of healthy subjects during a gait task (Timed Up and Go Test), which is very similar to what we will do by evaluating the variability of the COM during gait. Based on the data of Bonnyaud et al. [24], there was a difference of 99.5 cm in the trajectory lengths of the patients with stroke and the healthy subjects. In the present study, we hope to find a reduction in this difference following anodal tDCS; however, following placebo tDCS, there should be no difference. To determine the size of the sample of patients, we used the standard deviations of the patients with hemiparesis included in the study by Bonnyaud et al. [24].

In order to obtain a 50 to 60% reduction of the difference in COM variability between anodal and placebo tDCS with a power of 90% and a moderate to large effect size, a sample of 39 subjects is necessary. We therefore decided to include 40 patients in order to cover any drop outs. All the calculations were carried out using XLSTAT 2016® with a threshold of 90% power and a significance of *α* = 0.05.

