#### Analysis of outcome measures

Patient characteristics (age, gender, etc.) will be described by means, medians and standard deviations for continuous numeric parameters and by frequency tables with 95% confidence intervals for qualitative parameters.

A chi-squared test with Yates’ correction or the Fisher’s exact chi-squared test will be used to compare the distributions of qualitative variables.

There will be two possibilities for quantitative and ordinal variables:If the data are close to a normal distribution, means will be compared using Student’s *t* test

Comparison of the means or medians will be carried out for all the functional clinical data and the data determined following the movement analyses during the different evaluations. Repeated measures analysis of variance (ANOVA) and/or analysis of covariance as well as *t* tests (and/or non-parametric sign tests), corrected using the Scheffé adjustment, will be used for multiple comparisons.2.If the variables do not follow a normal distribution or if the small number of subjects studied does not allow the normality to be determined, we will use non-parametric tests such as Wilcoxon for the comparison of two variables, or Kruskall-Wallis for the comparison of more than two variables

All tests will be carried out with a bilateral threshold of first order of 5%.

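### In the non-normal branch the protocol names Kruskal-Wallis, an independent-groups test, for measurements repeated within the same cross-over patients

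*Protocol article*

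**What the plan says.** The Study design section describes a two-condition cross-over: "This is a prospective, randomised, placebo-controlled, cross-over, double-blind, single-centre study over a period of 36 months". Every patient has an anodal and a placebo visit, and "The order of the placebo and anodal tDCS visits will be randomised". The primary outcome is recorded once at inclusion and "then four times during the stimulation visits: before, during, immediately after and 30 min after cessation of stimulation". That makes 2 × 4 = 8 matched measurements per patient over the two stimulation visits.

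Analysis of outcome measures then splits quantitative and ordinal variables into two branches.

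- **Close to normal:** Student's t test, repeated-measures ANOVA and/or analysis of covariance, and t tests and/or sign tests with a Scheffé adjustment.
- **Not normal, or too few subjects to tell:** "we will use non-parametric tests such as Wilcoxon for the comparison of two variables, or Kruskall-Wallis for the comparison of more than two variables".

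The article does not say whether Wilcoxon means the signed-rank or the rank-sum test, or whether the t tests are paired. No rank test for repeated measurements on more than two occasions is named. Qualitative variables are handled in a separate sentence, directly after the description of patient characteristics: Yates' chi-squared or Fisher's "exact chi-squared test will be used to compare the distributions of qualitative variables".

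**The concern.** The rank counterpart of repeated-measures ANOVA is the Friedman test. Kruskal-Wallis is the counterpart of one-way ANOVA on independent groups. Under the protocol's own rule, a variable that fails the normality check therefore moves from a within-patient analysis to one that ignores the matching. Differences between patients, which the cross-over is meant to remove, go back into the error term.

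The branch could well be used. It covers ordinal variables as well as quantitative ones. The modified Ashworth and Medical Research Council scores are ordinal and are taken before and after stimulation at two visits, which gives four matched sets. Measures of variability cannot fall below zero, so skew in the primary outcome is plausible, although the protocol does not show it.

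What is at stake is a missed effect, not a false positive. This matters because the Discussion says that a null result with no other robust explanation would suggest that anodal tDCS has no effect on gait and balance.

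**Working it through.** **1. The protocol's sample size.** The Statistical analysis section states that "with a power of 90% and a moderate to large effect size, a sample of 39 subjects is necessary". It gives neither a numeric effect size nor an SD, so 39 cannot be reproduced, only solved backwards. For a paired t test, two-sided α = 0.05, 90% power, n = 39:

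- Normal approximation: dz = (1.960 + 1.282)/√39 = 0.519.
- Exact t calculation: dz = 0.533.

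The reference difference is 99.5 cm, so a 50 to 60% reduction is 49.75 to 59.7 cm. The implied SD of the within-patient differences is 49.75/0.533 = 93 cm to 59.7/0.533 = 112 cm. An effect of 0.533 fits the stated moderate to large description and is used below.

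**2. Type I error of Kruskal-Wallis on four matched sets.** Let ρ be the within-patient correlation, equal for all pairs of time points. The protocol gives no value, so ρ is an assumption and a range is shown. With no effect, the Kruskal-Wallis statistic in large samples behaves like (1 − ρₛ) times a chi-squared variable on 3 degrees of freedom, where ρₛ is the rank correlation. For normal data ρₛ = (6/π)·arcsin(ρ/2). The true error rate is then P(χ²₃ > 7.815/(1 − ρₛ)):

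- ρ = 0.3: ρₛ = 0.288; 7.815/0.712 = 10.97; P = 0.012.
- ρ = 0.5: ρₛ = 0.483; 7.815/0.517 = 15.10; P = 0.0017.
- ρ = 0.7: ρₛ = 0.683; 7.815/0.317 = 24.6; P below 0.0001.

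Simulation with n = 39 agrees: about 0.012 at ρ = 0.3, 0.001 to 0.002 at ρ = 0.5, and essentially zero from ρ = 0.7. Friedman stays at 0.045 to 0.056.

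**3. Power with the paired effect fixed.** Because dz = δ/(SD·√(2(1 − ρ))), the shift in units of the between-patient SD is 0.533·√(2(1 − ρ)). The simulation places this shift at all three later time points (n = 39, normal data, 3,000 replicates per setting).

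| ρ (assumed) | shift/SD | Kruskal-Wallis | Friedman |
|---|---|---|---|
| 0.3 | 0.631 | 0.81 | 0.85 |
| 0.5 | 0.533 | 0.60 | 0.84 |
| 0.7 | 0.413 | 0.21 | 0.85 |
| 0.8 | 0.337 | 0.04 | 0.85 |
| 0.9 | 0.238 | 0.00 | 0.85 |

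Repeat runs moved these figures by only 0.01 to 0.02. Lognormal data gave the same picture (Kruskal-Wallis 0.57 at ρ = 0.5 and 0.04 at ρ = 0.8).

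**4. Sensitivity to how the effect is fixed.** If the shift is held at 0.5 between-patient SD whatever ρ is, Kruskal-Wallis keeps 0.42 to 0.57 power, while Friedman rises from 0.47 (ρ = 0) to 1.00. If it is held at 0.744 SD, the effect that 39 per group would detect in an independent comparison, Kruskal-Wallis keeps 0.92 to 0.995.

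**5. Two conditions only.** With dz = 0.533, signed-rank Wilcoxon has power 0.88 to 0.89 at every ρ. Rank-sum Wilcoxon has 0.80, 0.65, 0.36 and 0.16 at ρ = 0.3, 0.5, 0.7 and 0.8. Leaving the type of Wilcoxon open therefore matters.

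**The case against.** The defence has several good points.

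- **The test list is illustrative.** It is introduced as a set of examples. But Kruskal-Wallis is the only test named for more than two sets of data, and no repeated-measures rank test appears anywhere, so this does not rescue the wording.
- **The authors intend within-patient analysis.** They name repeated-measures ANOVA and sign tests, and Wilcoxon may mean signed-rank. This stands: the simple anodal-placebo contrast need not lose any power. It does not help comparisons across more than two evaluations. Equally, the four-time-point simulation does not measure a loss on the two-condition contrast.
- **Some comparisons really are between patients.** Val66Met carrier status and functional level are examples, and independent-group tests are valid there. A reader might infer that every comparison in the plan is matched; the protocol does not support that.
- **Chi-squared and Fisher.** A reader might infer that these are prescribed for paired outcomes. The sentence follows the patient characteristics and assigns them to no anodal-placebo or before-after comparison. Obstacle contacts are recorded as a count, so they fall in the quantitative branch.
- **The error is conservative and its size rests on an unstated correlation.** Both are true. A reader might conclude that power nearly vanishes in this branch generally. That needs ρ of about 0.8 or more with the paired effect fixed; at ρ = 0.3 the loss is small.

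**Conclusion.** The point holds in a limited form. For comparisons of more than two evaluations within patients, the protocol names a test whose independence assumption the design violates, and it contradicts its own choice for normal data. This is a stated wrong choice, not a detail left to an analysis plan.

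The direction is certain for positively correlated measurements: the test rejects too rarely under no effect. The power loss ranges from slight (ρ about 0.3, or a large effect relative to the between-patient SD) to almost complete (ρ of 0.8 or more with dz about 0.53). These figures assume equal correlation between time points, an effect back-solved from n = 39, and correlations that the protocol does not supply. How often the branch would be used is also unknown.

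**What to change.** In the non-normal branch of Analysis of outcome measures:

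1. For within-patient comparisons of more than two evaluations, replace Kruskal-Wallis with Friedman, or with a repeated-measures model on suitably transformed data.
2. State that Wilcoxon between conditions or time points is the signed-rank test, and that t tests between conditions or time points are paired.
3. Keep Kruskal-Wallis, rank-sum Wilcoxon and chi-squared or Fisher for between-patient comparisons such as Val66Met carrier status or functional-level groups, and say so.
4. If any binary result is compared between conditions, use McNemar.

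The cost is wording only. No extra patients, visits or measurements are needed. The article reports the trial as ongoing, so the change should be made and dated before the treatment codes are opened.

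### No error control across several primary tasks and no named confirmatory contrast, while the planned Scheffé correction is not reflected in the sample size

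*Protocol article*

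**What the plan says.** **Primary measures.** The Primary outcomes section of the protocol article lists COM variability in gait, COM variability in trajectory tracking, and COP variability in static balance. Gait is recorded at comfortable and maximal speed, and static balance with eyes open and eyes closed, which makes five measures if each condition is analysed separately. Each is recorded once at inclusion, "then four times during the stimulation visits: before, during, immediately after and 30 min after cessation of stimulation". The main aim at the end of the Background also mentions gait initiation and obstacle crossing. No task, condition or time point is named as the one that decides the trial.

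**Analysis.** The section Analysis of outcome measures sets one level: "All tests will be carried out with a bilateral threshold of first order of 5" per cent. For near-normal data it offers repeated-measures ANOVA and/or analysis of covariance together with t tests (and/or sign tests), "corrected using the Scheffé adjustment, will be used for multiple comparisons". For other data it offers Wilcoxon or Kruskal-Wallis tests and states no correction.

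**Sample size.** The Statistical analysis section targets "In order to obtain a 50 to 60% reduction of the difference in COM variability between anodal and placebo tDCS", and finds that "with a power of 90% and a moderate to large effect size, a sample of 39 subjects is necessary". The calculation was done "with a threshold of 90% power and a significance of *α* = 0.05". It mentions neither Scheffé nor more than one outcome. It gives no numeric standard deviation and no numeric effect size.

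**The concern.** Two stated choices conflict with the rest of the plan.

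First, several measures carry primary status and each is tested at 5%. The Scheffé sentence concerns comparisons among evaluations; nothing in it combines tasks. With no confirmatory contrast named, a positive result on any one task, at any one time, could be reported as success on the primary outcome.

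Second, the trial is sized for one comparison at unadjusted 5%, while the normal-data branch corrects multiple comparisons with a method that protects every possible contrast. If that correction governs the deciding comparison, 39 patients do not give the stated 90% power.

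At stake are the meaning of a positive primary finding and the reliability of a negative one.

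**Working it through.** **1. The plan's own figure.** Inputs from the Statistical analysis section: 39 patients, power 90%, alpha 0.05. The analysis section makes the tests two-sided, and the cross-over design makes the comparison paired. With no standard deviation or numeric effect, 39 can only be back-solved.
- Paired t test: 90% power at n = 39 requires d = 0.533, so the noncentrality is 0.533 × √39 = 3.33.
- Normal formula: d = (1.960 + 1.282)/√39 = 0.519.
- For comparison, d = 0.5 needs 44 patients and d = 0.8 needs 19 (paired t).

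So 39 is consistent with one unadjusted two-sided paired comparison at d of about 0.52 to 0.53. This is consistency, not an independent reproduction.

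**2. Familywise error if any one success counts.** For m independent tests it is 1 − 0.95^m. For correlated tests, 200,000 sets of equicorrelated normal statistics were simulated with the cut-off |z| > 1.96.

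| Tests at 5% | m | Independent | Correlation 0.5 |
|---|---|---|---|
| Named measures | 3 | 1 − 0.8574 = 14.3% | 12.6% |
| With both speeds and both eye conditions | 5 | 1 − 0.7738 = 22.6% | 18.4% |
| Five conditions × three times during or after stimulation | 15 | 1 − 0.4633 = 53.7% | 36.1% |

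The first two rows are the across-task part and remain even if Scheffé fully controls the time points within each outcome. The third row applies only where time points are also uncorrected, which is the non-parametric branch.

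**3. Power if Scheffé governs the deciding contrast.** The critical value is c = √[(k − 1) × F0.95(k − 1, (k − 1)(n − 1))] for k means. Power comes from the noncentral t at n = 39, assuming that the deciding contrast has d = 0.533.

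| Family | k | F degrees of freedom | c | Power |
|---|---|---|---|---|
| One anodal-placebo contrast | 2 | 1, 38 | 2.02 | 90% |
| Four time means | 4 | 3, 114 | 2.84 | 68.7% |
| Eight condition-by-time means | 8 | 7, 266 | 3.78 | 32.8% |

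With n − 1 = 38 error degrees of freedom, the last two become 65.5% and 28.5%. With 40 patients they are 70.2% and 34.3% (pooled degrees of freedom). Restoring 90% would take 60 patients for k = 4 or 90 for k = 8.

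**4. A comparator.** Bonferroni over three tests (alpha 0.05/3 = 0.0167) gives 79.0% power at n = 39 and the same d.

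**The case against.** - **The 5% sentence sets level and sidedness; it does not say that tests are uncorrected.** This stands. A Scheffé-adjusted test is also run at 5%, and the Scheffé sentence follows directly on the comparison of movement-analysis data across evaluations. A reader might infer that time points are uncontrolled throughout and that 54% is the plan's general error rate. The text does not support that for the normal-data branch.
- **The 54% error rate and the Scheffé power loss cannot hold together.** This also stands. One assumes no correction over time points and the other assumes that it is applied. They belong to different branches.
- **The power loss is conditional.** This stands. The article never says that the deciding test is a pairwise contrast among four or eight means, and its and/or wording allows an ANOVA or ANCOVA test. The four-mean case applies the planned anodal-placebo effect to a family of time contrasts, which is an assumption. For two conditions Scheffé equals the unadjusted test.
- **No rule says that any one success suffices; the aims are joined by 'and'.** This is fair, and if all measures had to succeed the error rate would not inflate. But that rule is not stated either, and it would also miss the stated power: three independent measures, each with 90%, would all succeed with probability 0.9³ = 73%.
- **Such detail belongs in the SAP, and Scheffé is a valid method.** Partly right. Scheffé is conservative, not wrong, and the choice of ordering can sit elsewhere. But the article itself fixes several primary measures, the 5% level, the Scheffé correction and a sample size for one unadjusted comparison. The mismatch lies among those statements.

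**Conclusion.** The point holds in a limited form. The article names three primary measures (five by condition) without a confirmatory contrast, and states no error control across them. If any one success counts, the across-task familywise error is about 14% to 23% under independence and about 13% to 18% at correlation 0.5. In the non-parametric branch, where no correction is stated, it could reach 54% (36% at correlation 0.5) over 15 tests.

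The sample size does not reflect the Scheffé correction. Power would be about 69% or 33% instead of 90% only if the deciding test is a Scheffé contrast among four or eight means. Those figures rest on a paired test and a back-solved d of 0.53. It would go too far to say that the plan as a whole has 33% to 69% power, because a single anodal-minus-placebo contrast, which the wording permits, keeps 90%. What can be said is that the article does not settle which test decides the trial, so neither the 5% nor the 90% is secured.

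**What to change.** Name one anodal-minus-placebo contrast, for one outcome and one time point, as primary at two-sided 5% without correction. This is what the sample size assumes. Test the other tasks and time points in a fixed order or with Holm, and state that the rule applies in both the parametric and the non-parametric branch. If several primary measures are kept, or Scheffé is kept on the primary contrast, restate the power or the sample size accordingly; Bonferroni over three tests, for example, gives about 79% at 39 patients.

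The cost is a change of wording in the protocol and SAP, with no new patients or measurements. The article reports the trial as ongoing, so the change should be fixed and dated before unblinded data are examined. The downside is that under a fixed order, outcomes lower in the order can be claimed only if the earlier ones succeed.

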### Data monitoring

This research carries a level-B risk.

The clinical research associate (CRA), who represents the sponsor, will visit the investigating centre at a frequency that corresponds to the patient follow-up specified in the protocol. Several monitoring visits will be carried out:An opening visit in each centre: before the first inclusion, to set up the protocol and make acquaintance with the various participants involvedDuring the protocol: the Case Report Forms will be reviewed by the CRA. The principal investigator, who includes and follows the persons involved in the research, will accept regular visits from the CRA.o During these visits, and in accordance with the Good Clinical Practice, the following elements will be reviewed:
■ Compliance with the protocol and defined procedures for research■ Audit of informed consent by the patients■ Review of source documents and comparison with data reported in the Case Report Forms: accuracy of data, missing data, consistency of data according to the rules laid down by DRCD procedures
Closing visit: review and archiving of the biomedical research documents

